**What proportion of the cereals you have eaten today are whole grains?**			
	Whole grains	Scale 0-100: 0=no whole grains at all and 100=all cereals I ate were whole grains	
**What proportion of the oils and fats you have added to your food today is virgin or extra virgin olive oil?**			
	Virgin or extra virgin olive oil?	Scale 0-100: 0=no virgin olive oil at all and 100=all the added fat I consumed were virgin/extra virgin olive oil	
**Have you wasted food today? It includes foods that you discard for different reasons: expired foods, that have gone bad, leftovers both at home and in restaurants...**			
	Food waste	1=yes and 2=no	
**Do you want to comment or clarify any point? If you want to report any food that you have consumed that is not collected in the questionnaire, please, indicate the amount consumed as well.**			
	Comment or clarification	Open question	

**Figure 2 figure2:**
[figure not shown]
Screenshot of the item aimed at fruit and vegetables consumption.

##### Eating Behavior Scoring Procedure

In terms of the scoring procedure, we designed an index for assessing dietary healthiness and environmental sustainability for every assessment week based on 10 out of the 12 items provided in Table 1. The item related to white meat, eggs, and fish is not considered in the score to avoid overrating protein groups. However, it will be used in the individual food analysis to assess whether, in the case of a reduction in the consumption of red and processed meat and not a simultaneous increase in legume consumption, red and processed meat is replaced by animal-based proteins (objective 2.2). The second item not included in the present index is the one assessing food waste. This last item will be used as a specific outcome in itself and is not included in our main score.

Therefore, the environmentally sustainable healthy diet score is computed from 10 items, each of which is treated continuously from 0 to 1 point; for example, the scoring of red and processed meat consumption is as follows: 0 points for the consumption of >2 servings of red and processed meat and 0.25, 0.5, 0.75, and 1 points for the consumption of 1.5, 1, 0.5, and 0 servings per week, respectively. Food consumption will be assessed as the average daily food consumed during the entire assessment week. The scoring criteria and rationales are listed in Table 3. The total score of the environmentally sustainable healthy diet index will be the sum of the points for each item. Thus, the environmentally sustainable healthy diet index will range from 0 to 10 points, with 0 points being the lowest score in terms of environmentally sustainable healthy diet and 10 points being the highest (best) score (Table 3). Our overall scoring criteria are based on the recommendations of reference entities in the field of nutrition, mainly the EAT-Lancet Commission, Food and Agriculture Organization, and World Health Organization [25,40,41].

**Table 3 table3:** Environmentally sustainable healthy diet index: scoring criteria.

Item	What does it assess?	Scoring criteria^a^	Rationale
Red and processed meat	Average daily red and processed meat consumption	1 point: 0 serv/w^b^ (or <0.15 serv/d^c^) 0 point: >2 serv/w (or >0.29 serv/d)	Ideally, no red or processed meat should be consumed in a sustainable healthy diet; however, up to 2 servings of red meat per week is acceptable [25].
Dairy products	Average daily dairy product consumption	1 point: ≤1 serv/d 0 point: >2 serv/d	In a sustainable healthy diet, the optimal intake of dairy products should be at the lower end of the range 0 to 500 mL (milk equivalents) [25].
Legumes and soy	Average daily legume and soy product consumption	1 point: ≥1 serv/d 0 point: 0 serv/d	Plant-based proteins should be the main protein source in someone’s diet, for their own health and for that of the planet. At least 1 serving of legumes per day should be consumed in a sustainable healthy diet [25].
Fruits and vegetables	Average daily fruit and vegetable consumption	1 point: ≥5 serv/d 0 points: <1 serv/d	At least 5 servings of fruits and vegetable (in total) should be consumed per day [25]. Less than 1 serving per day will be scored as 0 points owing to their crucial daily consumption for a healthy diet.
Nuts (including peanuts)	Average daily nut consumption	1 point: 1-2 serv/d 0 point: 0 serv/d and ≥4 serv/d	Daily consumption of nuts is recommended owing to their health benefits. Indeed, they have been suggested even as a replacement for red meat. However, the quantity should be moderate, as some nut-tree crops are water, fertilizer, and pesticide intensive [15,25].
Sugary, salty, and ultraprocessed foods	Average daily sugary, salty, and ultraprocessed food consumption	1 point: 0 serv/w 0 point: >2 serv/w (or >0.29 serv/d)	These foods should be consumed as less as possible; ideally, they should be avoided or at least consumed no more than once a week [40].
Whole grains	Proportion of servings of whole grains in relation to the total servings of all grains	1 point: 100% whole grains 0 point: 0% whole grains	Whole grains should be prioritized over their refined versions [25].
Oils and fats	Proportion of servings of virgin or extra virgin olive oil in relation to the total added fat intake	1 point: 100% virgin or extra virgin olive oil 0 point: 0% virgin or extra virgin olive oil	Unsaturated and nonrefined oils, mainly virgin olive oil (extra or not) in our context, should be prioritized over other dietary fats [25].
Alcoholic drinks	Average daily alcoholic drink consumption	1 point: 0 serv/w 0 point: >2 serv/w (or >0.29 serv/d)	Ideally, no alcohol should be consumed. According to the World Health Organization, the impact of alcohol consumption on chronic and acute health outcomes is largely determined by the total volume of alcohol consumed [41].
Other beverages: sodas, juices, energy drinks, etc	Average daily consumption of other unhealthy drinks	1 point: 0 serv/w 0 point: >2 serv/w (or >0.29 serv/d)	These foods should be consumed as less as possible; ideally, they should be avoided or at least consumed no more than once a week [40].

^a^Scores will range proportionally from 0 to 1 points. For instance, 0 points will be assigned for the consumption of >2 servings of red and processed meat per week and 1 point for 0 servings per week; 0.25, 0.5, and 0.75 points will be assigned for the consumption of 1.5, 1, and 0.5 servings per week, respectively.

^b^serv/w=servings per week.

^c^serv/d=servings per day.

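### Table 3's daily cut for full marks on red and processed meat (0.15 servings a day, or 1.05 a week) conflicts with the proportional rule in the text and footnote a

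*Protocol article*

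**What the plan says.** All of this is in the protocol article, mainly under Eating Behavior Scoring Procedure.

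- **Table 3, red and processed meat row.** Full marks are set at "1 point: 0 serv/w^b^ (or <0.15 serv/d^c" and zero marks at "0 point: >2 serv/w (or >0.29 serv/d".
- **Scoring text above Table 3.** Red and processed meat is the worked example, with "0.25, 0.5, 0.75, and 1 points for the consumption of 1.5, 1, 0.5, and 0 servings per week, respectively".
- **Table 3, footnote a.** Attached to the scoring-criteria column, it repeats the example: "0.25, 0.5, and 0.75 points will be assigned for the consumption of 1.5, 1, and 0.5 servings per week, respectively".
- **Scale of the input.** "Food consumption will be assessed as the average daily food consumed during the entire assessment week".
- **Sibling items.** Three other Table 3 rows have the same upper cut of 2 servings a week: sugary, salty and ultraprocessed foods; alcoholic drinks; and other beverages. Each gives full marks at 0 servings a week and has no daily allowance.
- **Role of the index.** The Limitations section names the weekly score as the primary outcome.

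**The concern.** The row treats zero servings a week and anything under 0.15 servings a day as the same condition. They are not, because the daily figure admits a little over one serving a week. The row therefore disagrees with itself, with the text and with the footnote.

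Because intake enters as a daily average, the per-day figure is a natural one to program. Two analysts working from the same article could then compute different primary outcomes from the same data. The disagreement lies inside the range from 0 to 2 servings a week, the only range in which this item can move. Objective 1.1.b also names red and processed meat as a food group of particular interest. The protocol says code and data will be made open access, so others may well rescore the index.

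**Working it through.** **Inputs** (Eating Behavior Scoring Procedure, Table 3 and footnote a): full-mark daily cut 0.15 servings/day; zero-mark cut 2 servings/week, printed as 0.29 servings/day; text and footnote points of 1, 0.75, 0.5 and 0.25 at 0, 0.5, 1 and 1.5 servings/week. Table 2 records servings in half-serving steps.

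**Step 1: reproduce the plan's own points.** Write w for servings per week. The proportional rule is max(0, 1 - w/2).
- w = 0: 1
- w = 0.5: 1 - 0.25 = 0.75
- w = 1: 1 - 0.5 = 0.5
- w = 1.5: 1 - 0.75 = 0.25

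These match the text and footnote exactly.

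**Step 2: check the unit conversions.**
- Zero-mark cut: 2/7 = 0.286, which rounds to 0.29. This is correct.
- Full-mark cut: 0.15 x 7 = 1.05 servings/week. This is not 0.

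**Step 3: score by each rule, all seven days answered.** Table 3 does not say how points fall between 0.15 and 0.29 servings/day. I assume a straight line, (0.29 - d)/(0.29 - 0.15), where d is average daily servings.

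| Servings/week | d | Text and footnote a | Table 3 daily cut | Gap |
|---|---|---|---|---|
| 0 | 0 | 1 | 1 | 0 |
| 0.5 | 0.071 | 0.75 | 1 | 0.25 |
| 1 | 0.143 | 0.5 | 1 | 0.5 |
| 1.5 | 0.214 | 0.25 | 0.54 | 0.29 |
| 2 | 0.286 | 0 | 0.03 | 0.03 |
| 2.5 | 0.357 | 0 | 0 | 0 |

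The entries at 1.5 and 2 rest on the straight-line assumption. If the line ends at 2/7 instead of 0.29, they become 0.53 and 0. The entries at 0.5 and 1 need no such assumption.

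**Step 4: effect on change scores.**
- From 1 to 0 servings/week: +0.5 by the text, 0 by the daily cut.
- From above 2 to 1: +0.5 by the text, +1 by the daily cut.
- From above 2 to 0: +1 by both.

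The choice of rule can therefore shrink or enlarge an apparent improvement, depending on where the participant starts and ends.

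**Step 5: a missed day.** One serving over six answered days gives d = 1/6 = 0.167, which exceeds 0.15, so full marks no longer apply. The text's rule on the daily-average basis gives 1 - 7 x 0.167/2 = 0.42. The straight line gives (0.29 - 0.167)/0.14 = 0.88. The rules still differ, by 0.46.

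**The case against.** The strongest reply is that the intended rule is hardly in doubt. The text, the footnote and the row's own zero-servings entry agree, the footnote uses this very item as its example, and a single parenthetical dissents. That is a good reason to think the parenthetical is the slip, and it sets the direction of the repair. It does not remove the conflict. The dissenting figure is the only full-mark criterion stated per day, which is the scale on which intake is scored. It could also have been meant as a tolerance, since the row's rationale accepts up to two servings a week.

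It is also fair to say that the effect is limited. Only one item of ten is touched. Full marks at 1 serving a week require all seven days answered, whereas the incentive rule accepts six. Red and processed meat is analysed separately from daily raw data under objective 1.1.b, and that analysis does not use the index points. All of this stands.

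Two stronger readings are tempting and are not supported.

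- **The gap rivals the expected effect.** A reader might set 0.5 point against a small effect on the power simulation's SD of 2. That SD is for the random intercept, and the Discussion does not tie its expected small to medium effects to it. The comparison would also put the largest single-week gap for one person against a group mean.
- **The whole-grain and olive-oil items misfire too.** A reader might infer that a day with no cereals or no added fat must be answered 0 and scored as the worst diet. The share on such a day is 0/0. In "0=no whole grains at all and 100=all cereals I ate were whole grains" the upper anchor is as vacuously true as the lower one, and the olive-oil item has the same structure. No passage says such days are coded 0, and response instructions are in Multimedia Appendix 5, which is not shown.

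**Conclusion.** The inconsistency is real and concerns the definition of the primary outcome. By the daily cut, 0.5 and 1 serving a week score 1 point when all seven days are answered; by the text and footnote a they score 0.75 and 0.5. With responses in half-serving steps, the gap never exceeds 0.5 point on the 0 to 10 index. It arises only at weekly intakes above 0 and up to about 2 servings.

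The effect on a group mean will be smaller. It depends on how many participant-weeks fall in that range in each phase, which the protocol does not give. The 96% power is unaffected, because the simulation generated index values directly and did not score food items.

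A reader might infer that Table 3 plainly awards full marks to one serving a week. It does not: the row also says 0 servings a week, and the award follows only from the parenthetical and only with seven answered days. The documents favour the proportional rule but do not formally settle the matter. This is a correction that should be made before scoring, not a defect that undermines the pilot.

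**What to change.** State one rule for red and processed meat before the index is scored, and make the Table 3 row, the text and footnote a agree. The edit best supported by the text, the footnote, the row's own zero-servings entry and the three sibling items is to delete the daily parenthetical from the full-mark criterion and score

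points = max(0, 1 - 7 x average daily servings / 2).

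Writing it with the daily average keeps the plan's stated basis. A plain weekly sum would understate intake in weeks with a missed day. The sponsor should confirm that this is the intended rule. If a tolerance below 0.15 servings a day was meant, the text and footnote must change instead, and the scaling between 0.15 and 0.29 servings a day must be written down.

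The cost is one table edit and one line of scoring code. Nothing changes in the app or in data collection. Raw daily servings are recorded, so any weeks already collected can be rescored.

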##### Mechanisms of Action

Seven items capturing key psychological or motivational mechanisms of action that could potentially play a role in the adherence to sustainable healthy diets will be measured once during each assessment week (refer to objective 2.1 in the *Introduction* and *Statistics* sections). All items are presented in Table 4. Motives for purchasing or eating foods related to dietary sustainability and healthiness (ie, health, environment, affordability, and ethical) will be captured with 4 items adapted from eating motivation validated scales [42,43]. Another item, selected from a validated 12-item questionnaire, will be used to evaluate ecoanxiety, a construct that has been previously described as a relevant mediator of proenvironmental behavior changes [44]. Habit strength of purchasing and eating food while thinking about sustainability will be measured using an item adapted from the Self-Report Habit Index and Self-Report Behavioral Automaticity Index [45,46], and finally, self-efficacy toward following a sustainable healthy diet will be assessed using another item [47]. The comprehension of these questions was tested by following the same methodology as the one stated earlier for text message content.

**Table 4 table4:** Items for food-related motives, ecoanxiety, habits, and self-efficacy.

Category and name			Item		Answer options
**Motives**					
	Health	In the last 7 days, how important was the healthiness of your food when choosing what to eat?		VAS^a^ 0-10: 0=not important at all and 10=very important	
	Environmental impact	In the last 7 days, how important was the environmental impact of your food (ie, carbon footprint, water footprint, etc) when choosing what to eat?		VAS 0-10: 0=not important at all and 10=very important	
	Fair and ethical sources	In the last 7 days, how important was the working conditions of the producers or sellers of your food when choosing what to eat or where to buy?		VAS 0-10: 0=not important at all and 10=very important	
	Price	In the last 7 days, how important was the price of your food when choosing what to eat?		VAS 0-10: 0=not important at all and 10=very important	
**Ecoanxiety**					
	Ecoanxiety	Over the last week, how often have you felt nervous, anxious or on edge, when thinking about climate change?		VAS 0-10: 0=never and 10=almost everyday	
**Habit strength**					
	Habit strength	Selecting healthy foods with low environmental impact and from fair sources is something that I do automatically, without thinking about it		VAS 0-10: 0=totally in disagreement and 10=totally in agreement	
**Self-efficacy**					
	Self-efficacy	To what extent do you feel capable of following a sustainable healthy diet?		VAS 0-10: 0=not at all confident and 10=totally confident	

^a^VAS: visual analog scale.

#### Relevance of the Interventional Text Messages

Finally, when sending motivational and educational messages as part of the intervention, we will ask the participants to indicate whether the message is “useful, informative or motivating” or “not useful, not informative or not motivating” in a visual analog scale. This will help us refine our messages for future studies and also control for engagement with the messages, given that an absence of answers will indicate that the participants did not read the message.

#### Qualitative Measurements

We will conduct 3 semistructured qualitative interviews to gain a deeper understanding of the intervention’s effect as well as to assess the feasibility, delivery, and acceptability of the intervention beyond the collected quantitative information. We anticipate that the qualitative data will allow us to complement the quantitative data in a way that adequately captures the contextual, social, and cultural factors that determine the intervention’s efficacy and perceived influence.

The first interview will be performed at baseline (during the first 2 weeks; refer to Figure 1) to investigate the eating behaviors of the participants (ie, habitual diet; favorite foods; sources of food; frequency of eating out; and the cultural, social, and personal backgrounds that may determine their behaviors), explore aspects related to sustainable healthy diets (ie, conceptualization of a sustainable healthy diet, participants’ views on what should change in their daily lives to achieve such a diet, previous attempts to improve their diet, and measures implemented in those attempts), and explore participants’ expectations of the intervention and their motivation for participating in the study. The second interview will be held at the end of the intervention (month 7) to examine participants’ perceptions of the effectiveness of the intervention (ie, changes in their eating habits and behaviors and other changes beyond diet, such as variations in their well-being and weight) as well as potential mediators that may have influenced outcomes that were not observable in the quantitative part; determine whether the intervention has been feasible (ie, any difficulties with the app, problems completing the questionnaires, understandability of the text messages, etc); identify potential improvements to the intervention’s delivery; and examine participants’ views on its acceptability, which includes engagement with both the evaluations and intervention’s features and any other relevant practical aspects of the study that the participants would like to discuss. The third interview will be conducted at the end of the follow-up period (month 12) and will be less structured than the previous ones, depending on the outcomes for each participant. The objective of the third interview will be to evaluate the persistence of the acquired eating behaviors, focusing on the personal, social, and contextual facilitators and barriers that may influence the persistence of the outcomes over time, as well as the role of the intervention in this persistence. The interview guides are included in Multimedia Appendix 6.

The objectives and procedures of the interviews will be explained at the beginning of the study in the face-to-face meeting for installing the app, in which each participant will confirm their willingness to participate. The researcher who will conduct the interviews will contact them to schedule an interview at each of the 3 time periods. The same researcher will be in charge of all the interviews. The interviews will be conducted on the web using the preferred platform of the participants (Google Meet [Google LLC], Zoom [Zoom Video Communications Inc], Signal [Signal Messenger LLC], WhatsApp [Meta Platforms Inc], etc), will last between 45 minutes and 1 hour, and will be audio recorded. During the interviews, prompts and probes will be used to collect rich and comprehensive data. All interviews will be digitally recorded, anonymized, and transcribed verbatim. Audio files and transcripts will be imported into the NVivo software (QSR International), which will be used for the data analysis.

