At the methodological level, specific limitations of previous eating and proenvironmental behavior change interventions have also been repeatedly mentioned in the literature. They include the use of long, paper-based food frequency questionnaires that do not allow for frequent and dynamic assessment of the behavior change process [22], short or nonexisting follow-up periods that preclude the appreciation of long-term changes and potential forms of behavioral maintenance over time, and study designs inappropriate for testing causal relationships [23]. To build upon previous research, this pilot trial has been designed to promote individual behavior change for a sustainable healthy diet over a year with measurement bursts of daily eating behaviors digitally implemented through smartphones to better understand and monitor the behavior change process through the study [24].

The primary objectives of this study are as follows:

1.1 To evaluate the effectiveness of a pilot digital behavior change intervention promoting a more environmentally sustainable healthy diet (1.1.a) and relevant specific food outcomes related to dietary sustainability (1.1.b)

By sustainable healthy diet, we refer to a healthy dietary pattern with low environmental impact (objective 1.1.a), that is, incentivizing the consumption of fruits; vegetables; legumes; nuts; whole grains instead of their refined versions; unsaturated and nonrefined vegetable oils as main dietary fats; and water as the main beverage instead of others, such as sodas or alcoholic drinks, while promoting a reduction in the consumption of meat (especially red and processed meats), dairy products (especially cheese), sugar-added products, products high in salt, and ultraprocessed foods [25], with minimal food waste and the purchase of food from fair and ethical sources.

Specific food groups or relevant food-related outcomes that will be investigated closely (objective 1.1.b) include: the consumption of red and processed meat, fruits and vegetables, ultraprocessed foods, and dairy products, and food waste.

1.2 To examine the feasibility and acceptability of the intervention and collect relevant information for iteratively improving future interventions

The secondary objectives are as follows:

2.1. The identification of mechanisms of action, notably motivational ones, potentially mediating the effect of the intervention on behaviors

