##### Objective 1.2: Feasibility of the Intervention

This objective will mainly be investigated through the qualitative data analyses reported in the next section. Simple quantitative analyses will be conducted to examine the relevance of our motivational and educational messages (ie, scores provided to the text messages at the individual and collective levels). We also report the percentage of missing values for each measurement burst.

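### The primary feasibility objective rests mainly on interviews set by study period, with none tied to stopping, so its answer may lean towards completers

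*Protocol article*

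**What the plan says.** The Prior Work section lists objective 1.2 among the primary objectives: "1.2 To examine the feasibility and acceptability of the intervention and collect relevant information for iteratively improving future interventions". On the evidence for it, the data analysis section for objective 1.2 says: "This objective will mainly be investigated through the qualitative data analyses reported in the next section".

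The Qualitative Measurements section sets three interviews:

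- **Baseline.** For objective 1.2, its contribution is to "explore participants’ expectations of the intervention and their motivation for participating in the study", before any exposure to the intervention.
- **Second.** "The second interview will be held at the end of the intervention (month 7"). It is meant to "determine whether the intervention has been feasible (ie, any difficulties with the app, problems completing the questionnaires" and similar matters), and it also covers improvements to delivery, acceptability and engagement.
- **Third.** "The third interview will be conducted at the end of the follow-up period (month 12"). The text describes it mainly as an interview on whether changed eating behaviours persist. Table 1 adds acceptability.

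On scheduling, the interviewer "will contact them to schedule an interview at each of the 3 time periods".

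Two quantitative sources also serve objective 1.2. One is participants' ratings of the educational and motivational messages, where no answer is taken to mean that the message was not read. The other is completeness: "We also report the percentage of missing values for each measurement burst".

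**The concern.** The people who found daily app reporting or the messages least workable are the ones most likely to stop before month 7. Under the stated schedule, someone who stops during the intervention has by then given only an interview about expectations. The main evidence on feasibility could then come largely from those who stayed.

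This matters because the Conclusions section says the study will identify what hinders and what helps the intervention, as input to a full randomized controlled trial. A barrier serious enough to make someone leave is among the most useful things such a pilot can learn, and an exit account not taken at the time is hard to recover later.

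**Working it through.** The plan states no figure for objective 1.2 that could be reproduced; its power simulation concerns objective 1.1.a only. The check is a comparison of the stated schedule with the point at which a participant stops, followed by illustrative arithmetic.

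**Inputs from the article.** 21 participants, 7 per socioeconomic group; 2-week baseline, then a 22-week intervention; interviews at baseline, month 7 and month 12; messages on 2 days per week. No withdrawal rate is given.

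**Step 1: what each source yields for someone who stops during the intervention.**

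| Source | Content for objective 1.2 | Available from an early stopper? |
|---|---|---|
| Baseline interview | Expectations, motivation | Yes, but before exposure |
| Month-7 interview | Feasibility, difficulties, improvements, acceptability | Only if contacted and willing after stopping |
| End-of-study interview | Acceptability (Table 1) | Same condition, and later still |
| Message ratings | Usefulness of each message; non-response | Yes, up to stopping; no reasons |
| Missing values per burst | Completeness | Yes; pools withdrawal with skipped entries; no reasons |

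**Step 2: the delay if a stopped participant is still interviewed at the planned time.** Someone who stops in intervention week w waits about 22 − w weeks for the end of the intervention. The maximum is about 22 weeks, or 22/52 × 12 = 5.1 months.

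**Step 3: how many participants this could concern.** Let d be the assumed proportion stopping before month 7, independent between participants and equal across groups.

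- Expected number: 21 × d.
- Chance of at least one: 1 − (1 − d)^21.
- Chance that some group of 7 loses three or more: 1 − (1 − p)^3, where p is the binomial probability of 3 or more out of 7. This gives p = 0.026, 0.148 and 0.353 at d = 0.1, 0.2 and 0.3.

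| d (assumed) | Expected of 21 | At least one | Some group loses ≥3 of 7 |
|---|---|---|---|
| 10% | 2.1 | 89% | 7.5% |
| 20% | 4.2 | 99% | 38% |
| 30% | 6.3 | >99% | 73% |

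Each person without a post-exposure interview is 1/7 = 14% of that group's possible accounts.

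**Step 4: what a completer-only answer could look like (all inputs assumed).** Suppose 90% of completers find the intervention acceptable, and a proportion w of those who stop. Completers report 90%, while the figure for everyone enrolled is 0.9(1 − d) + w·d.

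| d | w = 10% | w = 30% | w = 50% |
|---|---|---|---|
| 10% | 82% | 84% | 86% |
| 20% | 74% | 78% | 82% |
| 30% | 66% | 72% | 78% |

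Steps 3 and 4 show the mechanism and a plausible range. They do not estimate the bias in this trial.

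**The case against.** The strongest reply is that the article never says early leavers go uninterviewed. The scheduling sentence sets no condition on continued use of the app. The interviews are remote and run outside the study app, so someone who stops answering questionnaires could still be interviewed at month 7. A journal article condenses the full protocol, withdrawal procedures are commonly left to that document and the consent form, and the interview guides are in an appendix that is not shown.

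Much of this stands. A reader might infer that those who withdraw are not heard at all; the documents do not support that, because contact after stopping is not ruled out. What remains is the stated timing. Even on the generous reading, a person who stopped early is asked about difficulties months afterwards.

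Three further inferences also go too far:

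- That missing values are the only sign of disengagement. Message ratings are requested through the intervention and analysed at individual level, so a lasting stop in one person's answers would show.
- That setting quantitative and qualitative findings side by side cannot help. The planned joint displays could expose favourable interviews next to falling response, though they could not supply the reasons.
- That the loss will fall on the low socioeconomic group. The Participants section says deprived populations might benefit less from digital delivery. That concerns effect, not dropout.

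It can also be said that the breakdown of missing values is a reporting detail. That is fair taken alone, but here it is part of the evidence for a primary objective and costs almost nothing.

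**Conclusion.** The point holds as a weakness in a stated design choice, not as a demonstrated bias. A primary objective depends mainly on interviews fixed by study period. Feasibility, difficulties and improvements are asked about only at month 7, and no interview is tied to stopping. Participants who leave during the intervention are likely to be under-represented or reached late, and the feasibility answer may lean towards completers. The quantitative sources show that people disengaged, but not why.

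The direction rests on the assumption that those who stop view the intervention less favourably than those who stay. The size cannot be computed. The figure of 2 to 6 of 21 rests on an assumed withdrawal rate of 10% to 30%, and the gap in acceptability on further assumed proportions. The change is worth making because it is cheap and fits within the interviews already planned.

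**What to change.** 1. **Qualitative Measurements.** Offer the second interview at the end of the intervention or when the participant stops, whichever comes first, as an optional contact with the same guide and the same interviewer. Check that the consent wording allows it.
2. **Objective 1.2 analysis.** Report how many of the 21 enrolled, and of each group of 7, gave each interview. Split missing values per burst into withdrawn and still enrolled but unanswered.

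The cost is a change of wording in the protocol and possibly the consent form, with no interviews beyond the three planned per person. There are two downsides. Some who withdraw will decline, so the gap narrows rather than closes. Interview timing will also vary between participants, so the time since starting the intervention should be noted when the accounts are compared.
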